## Abstract

**Introduction:**

Endometriosis is a chronic gynecological disease associated with pelvic pain, infertility, and reduced quality of life. Ovarian endometrioma is its most common manifestation. Although laparoscopic cystectomy is widely used, concerns regarding ovarian reserve have led to increasing interest in conservative approaches. Ultrasound-guided ethanol sclerotherapy (EST) has emerged as a minimally invasive alternative with potential benefits for symptom control and reproductive outcomes. The ESCOMA trial aims to evaluate the impact of EST compared with expectant management on quality of life in women with ovarian endometriomas.

**Methods and analysis:**

ESCOMA is a prospective, multicentre, randomised controlled trial comparing ultrasound-guided ethanol sclerotherapy with expectant management. A total of 288 women with ovarian endometriomas will be randomised in a 1:1 ratio. The primary outcome is change in quality of life at 6 months, assessed using the Endometriosis Health Profile-5 (EHP-5). Secondary outcomes include pain reduction, changes in pain-related biomarkers, ovarian reserve markers, cyst size reduction, reproductive outcomes, adverse events and complications, diagnostic accuracy, and healthcare costs. Analyses will be performed according to both intention-to-treat and per-protocol principles.

**Ethics and dissemination:**

The study was approved by the Clinical Research Ethics Committee of Hospital Universitari de Bellvitge (PR070/25). Written informed consent will be obtained from all participants.

**Clinical Trial Registration:**

ClinicalTrials.gov, identifier NCT06955221.

## Strengths and limitations of this study

First multicentre randomised clinical trial directly comparing ethanol sclerotherapy and expectant management for ovarian endometriomas.Primary outcome focused on quality of life, assessed with a validated and widely used tool (EHP-5).Inclusion of ovarian reserve markers and reproductive outcomes (pregnancy rates and time to conception) enhances the clinical relevance of the study; however, fertility outcomes will only be evaluated in the subgroup of women who express a desire for pregnancy, which reduces the sample size for these endpoints and may limit the statistical power to detect differences between groups.The additional assessment of healthcare costs provides valuable information on the health-economic impact of both treatment strategies.Although an open-label design may influence subjective outcomes such as quality of life, objective biomarkers and pregnancy outcomes are less susceptible to bias.

## Administrative information

Protocol version: v2.

## Introduction

Endometriosis is a chronic, inflammatory, estrogen-dependent gynecological disease that affects approximately 5%–10% of women of reproductive age (1, 2) and is associated with infertility in up to 40% of cases (3). Ovarian endometrioma is its most frequent manifestation, occurring in 15%–45% of affected women (4). In addition to infertility, chronic pelvic pain is one of the main clinical symptoms, often causing work absenteeism and a substantial impairment in quality of life (QoL) (1, 2).

The optimal management of ovarian endometriomas remains controversial, and treatment should be individualized according to symptoms, reproductive plans, ovarian reserve, and cyst characteristics (1, 5). When surgical treatment is indicated, laparoscopic cystectomy remains the reference surgical technique because of its effectiveness in reducing pain and recurrence. However, surgery may reduce ovarian reserve owing to the inadvertent excision of healthy ovarian tissue, which is particularly detrimental in women with an already compromised reproductive potential (6, 7). Furthermore, postoperative recurrence rates remain high, ranging between 15%–30% (8). These limitations have stimulated increasing interest in conservative treatment strategies aimed at preserving ovarian reserve while achieving adequate symptom control, particularly in women wishing to conceive (1).

Current management of ovarian endometriomas has progressively shifted towards more conservative and fertility-preserving approaches, including expectant management, medical therapy, and minimally invasive interventions (1, 9). Treatment decisions should be individualized based on symptom severity, cyst characteristics, ovarian reserve, and the patient's reproductive goals (1, 9). Expectant management may be considered for selected asymptomatic women with ovarian endometriomas. However, because untreated endometriomas may be associated with a progressive decline in ovarian reserve, regular monitoring of cyst size and ovarian reserve is recommended (9). For symptomatic women who are not seeking immediate pregnancy, hormonal therapy is considered the first-line conservative treatment and includes combined oral contraceptives, progestins, and gonadotropin-releasing hormone (GnRH) agonists with add-back therapy (1, 10). Combined oral contraceptives are widely used as first-line medical therapy for pain and symptom control in women with endometriosis. However, evidence regarding their effect on endometrioma size and ovarian reserve remains limited (1, 9–11). Among progestins, dienogest is currently considered the first-line long-term medical treatment for endometriosis because of its effectiveness in reducing pain and improving endometriosis-related symptoms, with increasing evidence supporting its role in the management of ovarian endometriomas (9, 11–14). GnRH agonists remain an effective option for pain and symptom control in selected women with endometriosis. In women who are not seeking immediate pregnancy after surgery, postoperative treatment has been associated with lower endometrioma recurrence rates. However, their long-term use is limited by hypoestrogenic adverse effects; and add-back therapy is recommended to improve tolerability and facilitate prolonged treatment (10, 15). Although these conservative approaches play a key role in the management of ovarian endometriomas, each has specific indications and limitations, and none provides a definitive treatment while preserving ovarian reserve in all patients (1, 9, 11). Therefore, there remains a need for fertility-preserving alternatives that effectively control symptoms while minimizing the impact on ovarian reserve, particularly in women wishing to conceive (1, 9).

In this context, ultrasound-guided ethanol sclerotherapy has emerged as a promising minimally invasive, fertility-preserving alternative for selected women with ovarian endometriomas (16, 17). Its minimally invasive nature, outpatient setting, and potential to preserve ovarian reserve make ethanol sclerotherapy an attractive option for selected women with ovarian endometriomas, particularly those wishing to preserve their fertility (7, 18–20). Current evidence suggests that ethanol sclerotherapy achieves recurrence rates comparable to laparoscopic cystectomy while offering lower procedural costs and favorable reproductive outcomes, particularly in women with diminished ovarian reserve undergoing assisted reproductive treatment (16, 18, 21–23). However, despite these encouraging results, high-quality evidence on the long-term effects of ethanol sclerotherapy on quality of life, ovarian reserve, and reproductive outcomes remains limited (7, 16, 17, 23). These remaining uncertainties highlight the need for randomised clinical trials to better define the role of ethanol sclerotherapy in the management of ovarian endometriomas and provide the rationale for the present multicentre randomised clinical trial (16, 17, 23).

Beyond reproductive outcomes, improving quality of life is a key objective in the management of endometriosis. The Endometriosis Health Profile (EHP-30 and its shorter version, the EHP-5), developed at the University of Oxford, is a validated and widely used patient-reported outcome measure for assessing the impact of endometriosis on quality of life (24, 25).

Accordingly, the ESCOMA trial aims to compare ultrasound-guided ethanol sclerotherapy with expectant management in women with ovarian endometriomas, with the primary objective of comparing quality of life. Secondary objectives include assessing pain, ovarian reserve, reproductive outcomes, the need for subsequent surgery, safety, and treatment-related healthcare costs.

## Objectives

### Primary objective

To compare the impact of ethanol sclerotherapy vs. expectant management on quality of life in women with ovarian endometriomas, assessed with the EHP-5 questionnaire at baseline and at 6 months.

### Secondary objectives

To compare pain reduction between groups, measured by the Visual Analogue Scale (VAS) at 6 months and time to improvement.To assess changes in pain-associated biomarkers in serum [cortisol, C-reactive protein (CRP), interleukin-6 (IL-6)] and urine (cortisol, adrenaline, noradrenaline) between baseline and 6 months.To evaluate changes in ovarian reserve markers, including serum Anti-Müllerian Hormone (AMH) and antral follicle count (AFC), between baseline and 6 months.To compare the reduction in cyst size (largest diameter) between baseline and 6 months.To assess reproductive outcomes among women with pregnancy desire during the 24-month follow-up, including spontaneous pregnancies, assisted reproductive technology (ART) pregnancies, number of ART cycles required, and oocyte yield.To compare the number and type of adverse events and complications between groups.To identify the number of misdiagnosed cysts (non-endometriomas) in the sclerotherapy group.To compare treatment-related healthcare costs between groups.To assess endometrioma recurrence or progression during the 24-month follow-up.

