#### Procedure

Analgesic treatment is administered before the procedure, consisting of ibuprofen 1 h before and diazepam ½ hour before. On the day of the puncture, the patient must not present purulent leucorrhoea or genital bleeding.A single puncture is performed, preferably via the vaginal route, although an abdominal approach may be used if required by the patient's condition or by the cyst's characteristics, for example in virginal patients or when marked vascularization is observed along the puncture pathway.The abdominal wall or vaginal canal is disinfected with a povidone–iodine solution.A sterile 17-gauge needle (BD Medical Franklin Lakes, NJ, Becton, Dickinson and Company) is used. Under ultrasound guidance, the needle is advanced into the centre of the cyst and connected, through an extension tube and a three-way stopcock, to a vacuum aspiration system.Aspiration of the endometrioma contents may require dilution with saline solution (SS) when the fluid is thick. The aspirated fluid is measured using a syringe or an adapted measurement system.After nearly complete aspiration, several washes with Saline solution (SS) are performed until clear fluid is obtained.A volume of 100% ethanol equivalent to two-thirds of the aspirated volume is then instilled into the cyst, without exceeding 100 mL.The ethanol is left in place for 15 min without moving the needle, which remains inside the cyst.Subsequently, the cyst is emptied and washed twice with SS, using the same volume as the instilled ethanol.The aspirated fluid is sent to the pathology department for cytological examination to confirm the absence of atypical cells.The 100% ethanol solution used at all participating centres will be identical. The product will be supplied by *Farmacia Carreras*, the authorized provider for hospitals throughout Spain, ensuring consistency and avoiding potential bias related to variations in preparation.

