#### Expectant management group

Participants will continue the treatment they were receiving before study inclusion, or no treatment if none was previously prescribed. During follow-up, medical treatment may be initiated or modified according to clinical circumstances, patient preference, and usual clinical practice. Recommendations are provided to investigators to promote consistency in the management of the expectant-management group across participating centres (Supplementary Appendix 3); however, treatment decisions are not mandated by the study protocol. All concomitant treatments and subsequent changes will be prospectively recorded in the study database. Analgesia and supportive care are permitted in both groups. To minimize potential imbalance in this relevant clinical factor, randomisation will be stratified according to the presence or absence of concomitant hormonal treatment at study inclusion. In addition, the potential effect of hormonal treatment received during follow-up will be accounted for in the statistical analysis, including appropriate adjusted and sensitivity analyses.

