### Blinding

This is an open-label, non-blinded study. Both physician and patient will be aware of the allocated treatment arm, since blinding is not considered feasible when comparing an interventional procedure (EST) with expectant management according to standard clinical practice. The absence of blinding may influence patient-reported quality of life outcomes; however, it should not affect reproductive or biomarker outcomes, which are objective measures.

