### Statistical analysis

Primary analysis will use mixed linear regression models with clustering by patient to compare QoL scores. Secondary analyses will include chi-square for categorical outcomes, repeated measures ANOVA, Kaplan–Meier survival curves for pregnancy rates, and Mann–Whitney U tests for oocyte counts. Analyses will be performed on both intention-to-treat and per-protocol populations. A statistical analysis plan will be finalised prior to database lock.

Secondary outcomes will be analysed as defined in Supplementary Table S1. Continuous outcomes (e.g., VAS, AMH, AFC, cyst diameter, oocyte yield, biomarker levels) will be compared between groups using appropriate parametric or non-parametric tests depending on distribution. Categorical outcomes (e.g., pregnancy rates, adverse events, misdiagnosis) will be compared using *χ*^2^ or Fisher's exact test. Time-to-event outcomes (e.g., time to clinical improvement, time to spontaneous pregnancy) will be analysed using Kaplan–Meier curves and log-rank tests. Effect estimates will be presented with 95% confidence intervals. A detailed Statistical Analysis Plan is provided in the Supplementary Appendix S7.

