The economic evaluation of the ESCOMA study will compare direct medical costs between treatment groups, including healthcare resource utilization and the management of treatment-related complications. This will allow us to assess the healthcare costs associated with EST compared with expectant management.

Some limitations should be considered when interpreting the results of this study. First, the open-label design may influence patient-reported outcomes such as quality of life and pain perception. However, blinding is not feasible when comparing an invasive procedure with expectant management, and several secondary outcomes, including biomarkers, ovarian reserve parameters, and reproductive outcomes, are objective measures less susceptible to observer bias. Second, variations in clinical practice among participating centres may introduce heterogeneity. Nevertheless, the multicentre nature of the study enhances the external validity and generalizability of the findings. Third, reproductive outcomes will be evaluated only among women who express a desire for pregnancy, reducing the effective sample size for fertility-related analyses. Finally, although the primary endpoint will be assessed at 6 months, patients will be followed for a total of 24 months, allowing longer-term assessment of endometrioma recurrence or progression, reproductive outcomes, and subsequent interventions.

In conclusion, the ESCOMA trial has the potential to generate high-quality evidence regarding the role of EST in the management of ovarian endometriomas. By integrating patient-reported outcomes, reproductive outcomes, biological markers, and economic analyses, this study may contribute to redefining treatment algorithms and informing future clinical guidelines for women affected by this common and challenging condition.

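### The between-arm change in antral follicle count may mix ovarian reserve with follicle visibility, because only sclerotherapy empties the cyst; the reserve conclusion should rest on AMH

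*Protocol article*

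**What the plan says.** In the protocol article, Secondary objectives lists "To evaluate changes in ovarian reserve markers, including serum Anti-Müllerian Hormone (AMH) and antral follicle count (AFC), between baseline and 6 months". The same list has a second imaging outcome over the same interval: "To compare the reduction in cyst size (largest diameter) between baseline and 6 months". Under Statistical analysis, AFC and AMH are handled alike: "Continuous outcomes (e.g., VAS, AMH, AFC, cyst diameter, oocyte yield, biomarker levels) will be compared between groups using appropriate parametric or non-parametric tests".

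The Inclusion Criteria require a cyst of 30 to 100 mm and admit bilateral disease. In the sclerotherapy arm the cyst is aspirated and filled with ethanol for 15 minutes, after which the Procedure section says: "Subsequently, the cyst is emptied and washed twice with SS". For the comparator, the Expectant management group section says: "Participants will continue the treatment they were receiving before study inclusion, or no treatment if none was previously prescribed". Medical treatment may be started or changed there during follow-up.

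On measurement bias, the Discussion says that "several secondary outcomes, including biomarkers, ovarian reserve parameters, and reproductive outcomes, are objective measures less susceptible to observer bias". The Blinding section says of the open-label design that "it should not affect reproductive or biomarker outcomes, which are objective measures". The Discussion also says that a small effect on reserve would count in favour of sclerotherapy. Definitions, timing and aggregation of the secondary outcomes are left to Supplementary Table S1, and the detailed analysis to Appendix S7. Neither is shown.

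**The concern.** AFC is a count of the small follicles that can be seen. At baseline the counted ovary also holds a cyst of at least 30 mm. By 6 months one arm has had that cyst emptied and the other has not, and the trial plans to compare how far it has shrunk. If a cyst hides follicles, the counting conditions at 6 months depend on the allocated arm.

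Randomisation balances the arms at baseline but does not remove a distortion that the treatment itself causes. A reader blind to allocation would not remove it either, because the image has changed. The distortion would tend to raise AFC after sclerotherapy. Two misreadings could follow: better visibility taken for preserved reserve, or a real ethanol-related loss of follicles cancelled by follicles that have become visible. The second bears on safety, and sparing the ovarian reserve is part of the article's case for the procedure.

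**Working it through.** **The plan's own figure.** The article gives no AFC figure: no SD, no expected difference and no power. The only number to take over is the size of the arms.

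- Inputs (Sample size): rates 0.5525 and 0.715, two-sided α 0.05, power 0.80, 5% loss, arcsine method.
- h = 2·asin(√0.715) − 2·asin(√0.5525) = 0.3393.
- n = 2(1.960 + 0.842)² / 0.3393² = 136.4, so 137 per arm.
- 136.4 / 0.95 = 143.5, so 144 per arm, as stated.

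About 137 women per arm are therefore expected to be evaluable (144 × 0.95 = 136.8).

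**Assumed size of a visibility artefact.** None of these inputs is in the documents:

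- 4 to 6 countable follicles in the cyst-bearing ovary;
- 10% to 40% of them hidden at baseline, and regained only after sclerotherapy;
- SD of AFC change about 5.

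Artefact = follicles × hidden fraction: 4 × 0.1 = 0.4 up to 6 × 0.4 = 2.4 follicles. Divided by 5, this is 0.08 to 0.48 SD.

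**False-positive rate with no true effect on reserve.** For a standardised artefact d and n = 137 per arm (normal approximation):

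P(reject) = Φ(d√(n/2) − 1.96) + Φ(−d√(n/2) − 1.96), with √(137/2) = 8.277.

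| d | d × 8.277 | P(nominally significant) |
|---|---|---|
| 0.1 | 0.828 | 0.131 |
| 0.2 | 1.655 | 0.380 |
| 0.3 | 2.483 | 0.699 |

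**Sensitivity to the assumed SD.** Same formula, with d = gain / SD:

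| Gain in the sclerotherapy arm only | SD 3 | SD 5 | SD 7 |
|---|---|---|---|
| 1 follicle | 0.79 | 0.38 | 0.22 |
| 2 follicles | 1.00 | 0.91 | 0.66 |

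**Masking of a true loss.** Suppose sclerotherapy costs 2 follicles. The observed difference is then the visibility gain minus 2.

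| Visibility gain | Power, SD 3 | SD 5 | SD 7 |
|---|---|---|---|
| 0 | 1.00 | 0.91 | 0.66 |
| 1 | 0.79 | 0.38 | 0.22 |
| 2 | 0.05 | 0.05 | 0.05 |

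The tables show what would follow if the artefact had a given size. They are no evidence that it has that size, or that it exists.

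**The case against.** The strongest objection is that the mechanism is not in the documents. Nowhere do they say that an endometrioma hides follicles or that counting improves after sclerotherapy. That stands: the point is conditional on a general ultrasound premise.

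The contrast between arms is also a limiting case. Emptying happens on the day of the procedure, cyst size at 6 months is still to be measured, recurrence is an outcome, and women in the expectant arm may receive medical treatment. This stands too. It limits the likely size but not the direction, because only one arm has a procedure on the cyst.

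A reader might infer that the article gives AFC and AMH equal weight. It does not say so; it lists both without ranking them. Where the Discussion describes damage to reserve from surgery, the marker it names is AMH.

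A reader might also infer that the Discussion is wrong to call reserve parameters objective. That sentence speaks of observer bias, and treatment-dependent visibility is a different problem. The sentence is incomplete as reassurance, not false. The Blinding section refers to biomarkers and does not say whether AFC is among them.

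Finally, Table S1 or Appendix S7 may already set a rule for counting by ovary or for interpretation. Its absence cannot be asserted. The point rests on what the article does fix: AFC change as a between-arm reserve outcome. Counting by ovary would show where an artefact sits but would not remove it from the treated ovary, and women with bilateral cysts have no cyst-free ovary for comparison.

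**Conclusion.** The point holds as a conditional one. The article makes AFC change a between-arm reserve outcome while only one arm has the cyst in the counted ovary emptied. If cysts hide follicles, the contrast mixes reserve with visibility and would tend to favour sclerotherapy. The size is unknown. Under assumed artefacts of 0.1 to 0.3 SD, the nominal false-positive rate is 13% to 70%, and a visibility gain equal to a true loss leaves only the 5% error rate for detecting that loss.

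It would go too far to conclude that the reserve objective as a whole is compromised, or that AFC is known to be biased here. Serum AMH is measured at the same times and does not depend on what a scan can show, so only conclusions drawn from AFC are exposed. The primary endpoint, EHP-5 at 6 months, is unaffected. This is an inexpensive improvement in how a secondary result will be read, not the correction of a contradiction.

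**What to change.** First check Supplementary Table S1 and Appendix S7 for an existing rule. If there is none, make these changes before any comparative data are seen:

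- State that the ovarian-reserve conclusion rests on serum AMH, with AFC as supportive.
- Where AFC is recorded by ovary, show it separately for cyst-bearing and other ovaries. The article does not say how AFC is recorded, so this depends on the data collection.
- State that an AFC gain after sclerotherapy is not read on its own as preserved reserve.
- Add to the limitations in the Discussion that the objectivity of reserve parameters answers observer bias, but not a change in follicle visibility caused by treatment.

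The cost is wording, since AMH is already measured at baseline and 6 months. The downside is that AFC no longer supports a reserve claim by itself. The gain is that if AMH and AFC disagree, the choice between them will have been made in advance.
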